### Reporting of Serious Adverse Events (SAE)

Serious adverse events (SAE) are reported to the sponsor, via fax to Kliniskt Forskningscentrum Umeå, on a special SAE form within 24 hours of the investigator (or any other study staff) being informed of the SAE. The investigator determines if the event meets the protocol definition of an SAE, assesses causal relationship and intensity of the event. All SAE are reported to the sponsor independent of causality. The sponsor decides if the SAE fulfills the SUSAR criteria, and if so, is responsible for notifying the regulatory authorities (for SUSAR timelines see section 9.3.2).

Follow-up information describing the outcome and handling of the SAE is reported, via fax to Kliniskt Forskningscentrum Umeå, as soon as this information is available. The original should be kept in the Investigator Site File.

### Reporting of Suspected Unexpected Serious Adverse Reactions (SUSAR)

Those SAE which are assessed by sponsor to be SUSAR are reported via a [CIOMS form](https://cioms.ch/wp-content/uploads/2017/05/cioms-form1.pdf) to the European Medicines Agency (EudraVigilance database) according to the specified time frames.

SUSAR that are fatal or life-threatening are reported as soon as possible and no later than 7 days after the incident has become known to the sponsor. Relevant follow-up information is sent thereafter within an additional 8 days. Other SUSAR are reported as soon as possible and no later than 15 days after they have come to the sponsor’s knowledge.

Information about SUSAR occurring during the study is compiled by the sponsor and sent out to the principal investigator at all participating centers.

## Follow-up of Adverse Events

All reported SAEs that have not been resolved by the end of the study will be followed up until the event has subsided (or disappeared), the condition has stabilized, the event is otherwise explained or the study subject is lost to follow-up. SAE occurring after trial termination must be reported if considered related to the treatment during the trial.

## Independent Data Safety and Monitoring Committee (DSMB)

An advisory committee with 4-5 members will meet with the study board every week until 45 patients have been followed for at least 3 weeks and there after based on the decision of the DSMB, but at least once monthly until 100 patients has been included and followed. DSMB shall be eligible to stop randomization for safety reasons. They will meet by video conference.

This committee will advise the steering group in recommending possible extensions of the study and changes/amendments in the protocol. The DSMB may also be asked for advice in other questions brought up by the steering board.

## Annual Safety Report (Development Safety Update Report, DSUR)

A yearly safety report will be sent to the Swedish Medical Products Agency and the Swedish Ethical Review Authority. The safety report will summarize all serious adverse events recorded during the year, as well as a summary assessment of the safety of patients and if the risk-benefit assessment has changed.

## Procedures in case of emergencies, overdose or pregnancy

The sponsor and investigator will immediately take the urgent safety measures necessary to protect the subjects from immediate danger. The sponsor will inform the Swedish Medical Products Agency and EPM as soon as possible about the urgent safety measures taken by the investigator or sponsor.

If a study subject who participates in the trial becomes pregnant, this person must be followed up until the birth has taken place. If the fetus/child has any congenital malformation, this must be reported as a serious adverse event or side effect (SAE).

## Reference Safety Information

SPC for Enzalutamid will be used for reference safety information regarding assessment of whether an adverse event/incident (AE) is expected or not.

For updated SPC see Fass.se (<https://www.fass.se/LIF/product?userType=0&nplId=20160310000078>)

## Enzalutamide safety information in summary

Enzalutamide (Xtandi^®^, Astellas Pharma, film-coated tablet) is an androgen receptor inhibitor used in patients with prostate cancer and has a beneficial tolerance with few side effects in men and has also been tested in breast cancer patients in a few clinical trials with no more side effects compared to known side effects. Over 12000 men (2018) have been given enzalutamide in different clinical trials and it has been used as second and third-line treatment for prostate cancer in Europe and US since 2012.

For detailed information we refer to [www.fass.se](http://www.fass.se)

# Statistics

## Analysis population

Two efficacy analysis sets will be used: the ‘all patients treated’ set which will be analyzed according to the intention-to-treat (ITT) principle and it is therefore called the ITT set and the ‘per protocol’ (PP) set. The primary and secondary statistical analysis will be based on the ITT set. In addition, an analysis of the efficacy variables will also be carried out on the PP set in order to detect any sensitivity in the results obtained from the ITT analysis. At the clean file meeting it will be decided whether a patient will be included in the ITT and/or PP population. Also, a safety analysis set will be used for the assessment of the safety variables.

***The ITT analysis set***
All randomized subjects will be included in the ITT analysis set.

***UThe PP analysis set***
All subjects from the ITT set with no major protocol deviations and who have completed at least 8 cycles of treatment according to the protocol.

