## Treatment duration

The treatment with enzalutamide will start at randomization once daily in the hospital. Patients randomized to the experimental arm will receive the investigational product for the 5 days.

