# Study treatments

## Description of investigational product(s)

The investigational product is enzalutamide (Xtandi^®^, manufacturer Astellas Pharma Ab), 40 mg film-coated tablets. The patients are treated for five consecutive days, 4 tablets once a day each day, during the hospitalization period. The control group is treated with standard of care.

The investigational product is provided by the manufacturer Astellas Pharma Ab. The investigational product is ordered from the hospital pharmacy according to the clinic´s normal routines and taken from the clinic´s shelf. If changes take place between wards, local routines will be adopted.

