## Packaging, labeling, and handling of investigational products(s)

The investigational product is an approved medicinal product (Xtandi^®^) in Sweden. The package currently marketed in Sweden, 4x28 film-coated tablets in blister, is used in the trial. Xtandi^®^ is ordered from the hospital pharmacy according to the clinic´s normal routines and stored in the clinic´s shelf according to the clinic´s normal routines. No additional labelling for clinical trial is used. Discharged patients or patients transferred to ICU will not continue with enzalutamide treatment.

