## Drug accountability and treatment compliance

Drug accountability will be registered everyday (day 0-4), and treatment compliance will be registered in the CRF.

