## Treatment after study end

The treatment period with investigational product in this trial is 5 days or until discharge from the hospital or need of mechanical ventilation, whichever occurs first. After day 7 there is no restriction of medical treatments or inclusion in studies for any experimental therapies. If the patient is stopping treatment of enzalutamide earlier due to any cause, there are not restrictions for after treatments.

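### The per-protocol set requires 8 treatment cycles in a trial with a single course of at most 5 days, so as written it contains no patients

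*Protocol*

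**What the plan says.** Section 10.1 (Analysis population) bases the primary and secondary analyses on the ITT set, which is all randomized subjects. It then commits to a second look: "an analysis of the efficacy variables will also be carried out on the PP set in order to detect any sensitivity" in the ITT results. Under the PP heading, that set is limited to ITT subjects with no major protocol deviation "who have completed at least 8 cycles of treatment according to the protocol".

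The treatment sections describe one short course:

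- Treatment duration: "Patients randomized to the experimental arm will receive the investigational product for the 5 days".
- Description of investigational product(s): "The patients are treated for five consecutive days, 4 tablets once a day each day, during the hospitalization period". The same section gives the control group standard of care.
- Drug accountability and treatment compliance: "Drug accountability will be registered everyday (day 0-4").
- Treatment after study end: dosing lasts "5 days or until discharge from the hospital or need of mechanical ventilation, whichever occurs first".
- Packaging, labeling, and handling: "Discharged patients or patients transferred to ICU will not continue with enzalutamide treatment".

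The abbreviation list also defines PP. That definition has no cycle count and demands complete adherence with no deviation of any kind.

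**The concern.** The PP rule is a stated criterion that fails when followed; it is not a detail left for the SAP. It counts treatment in a unit the protocol never defines and sets a threshold the dosing schedule cannot reach. The only sensitivity analysis stated in this document then has no patients.

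Someone will have to replace the rule. Section 10.1 leaves the assignment of patients to sets to the clean file meeting. If the text is not corrected first, that meeting must invent the rule after data collection, in a trial that is not blinded. The natural improvisation, reading 8 cycles as all five doses, would tie membership of the set to the two primary endpoints in one arm only.

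**Working it through.** **Can anyone qualify?** The threshold is 8. The maximum attainable count follows from the schedule:

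| Meaning given to a cycle | Enzalutamide arm, maximum | Control arm, maximum | Reaches 8? |
|---|---|---|---|
| The 5-day course | 1 | 0 | No |
| One daily dose (days 0 to 4) | 5 | 0 | No |

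With 2:1 allocation, the numbers qualifying are:

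- N = 45: 0 of 30 and 0 of 15.
- N = 100: 0 of about 67 and 0 of about 33.
- N = 600: 0 of 400 and 0 of 200.

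The text does not restrict the condition to the enzalutamide arm. If it were read that way, PP would hold controls only, and there would still be no comparison.

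**Would all five doses serve instead?** The fifth dose falls on day 4. A patient on enzalutamide who is discharged or ventilated before then stops because the protocol says so, yet would be excluded. A control patient with the same course would be kept. Discharge, and ventilation or death, are the two primary endpoints.

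The effect of this can be shown under no treatment effect. Let *p* be the proportion who have ventilation or death, *a* the probability that such a patient is still on treatment at day 4, and *b* the same probability for the others. The event proportion among retained enzalutamide patients is

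*p·a* / (*p·a* + (1 − *p*)·*b*), against *p* in controls.

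The protocol gives none of these inputs. As assumptions, take *p* = 20%, exponential event times with mean *m*, and discharge at 1 day plus an exponential time with mean *d*. Ignore the 30-day limit. Then *a* = exp(−4/*m*) and *b* = exp(−3/*d*).

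| *m* (days) | *d* (days) | *a* | *b* | Enzalutamide, retained | Control | Ratio |
|---|---|---|---|---|---|---|
| 3 | 9 | 0.264 | 0.717 | 8.4% | 20% | 0.42 |
| 7 | 9 | 0.565 | 0.717 | 16.5% | 20% | 0.82 |
| 14 | 3 | 0.751 | 0.368 | 33.8% | 20% | 1.69 |

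For example, in the second row 0.2 × 0.565 = 0.113, 0.8 × 0.717 = 0.573, and 0.113 / 0.686 = 16.5%. The ratio is below 1 when *a* < *b* and above 1 when *a* > *b*. Under the second row, the mean time to discharge among patients without an event would be 4 + 9 = 13 days in retained enzalutamide patients and 1 + 9 = 10 days in controls. That is an apparent harm on the other primary endpoint.

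**Are the surrounding texts consistent?** Two pairs are not:

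- The abbreviation list excludes patients with any deviation, while section 10.1 excludes only those with a major one.
- Packaging, labeling, and handling ends dosing at discharge or ICU transfer, while Treatment after study end names discharge or need of mechanical ventilation. A patient moved to the ICU without ventilation is treated differently by each, so adherence up to the permitted stop has no single meaning.

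**The case against.** The strongest reply is that this is leftover wording with little consequence. The primary and secondary analyses use all randomized subjects. Nothing in the protocol ties the sample size, the interim look or the safety analysis to the PP set. The condition is so plainly unusable that it could not bias a result unnoticed, and the abbreviation list already offers a definition without a cycle count. All of this stands as to severity. It does not make the rule usable: the operative definition is the one in section 10.1, and the abbreviation list differs from it on deviations as well.

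A second reply is that the clean file meeting will sort it out. That meeting can apply a rule. Here it would have to write one, with the data collected and the allocation known.

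A reader might go further and infer that a careless repair would create a large false benefit, such as a halved hazard of ventilation or death. The documents do not support that. They propose no repair, and they give no event rate, event timing or length of stay. The illustration above runs from an apparent benefit to an apparent harm as those assumptions change. A reader might also infer that the controls are untreated, or that the trial has no other sensitivity analysis. Controls receive standard of care, and the SAP, which is not at hand, may contain more.

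**Conclusion.** The PP definition is wrong as written. It contradicts the protocol's treatment schedule, and 0 patients in either arm meet it at any planned sample size. That count follows from the text and needs no assumption. The consequence is limited to the PP sensitivity analysis of the efficacy variables, which cannot be run; the ITT results stand. It should be fixed, but it is not a fault in the primary analysis.

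The warning against an all-five-doses rule rests on its structure: it selects on the primary outcomes in one arm only. No size or direction of bias can be given from this protocol, nor can the size of a corrected PP set, because deviation and early-stop rates are not stated.

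**What to change.** In section 10.1, delete the 8-cycle condition and define PP as ITT patients with no major deviation from a list fixed before data review, plus:

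- **Enzalutamide arm:** study drug taken as scheduled up to the earlier of the end of the 5-day course or a stop that the protocol specifies.
- **Control arm:** no enzalutamide taken.
- **Both arms:** a patient who stops because the protocol requires it remains in PP.

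Do not substitute a requirement for all five doses.

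Two reconciliations belong with this change. The abbreviation list and section 10.1 should agree on whether any deviation or only a major one excludes a patient. The sections on packaging and handling and on treatment after study end should give one statement of when dosing stops, so that the adherence rule can refer to it. Which statement is right is for the sponsor to decide.

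The cost is a short text change in section 10.1 and consistent wording in three other places. No new data are needed, since drug accountability is already recorded daily on days 0 to 4.

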***USafety analysis set***
All randomized subjects will be included in the safety analysis set. This set is identical to the ITT set.

- 1. Statistical analyses

### 10.2.1 Statistical methods

### Summary statistics

Clinical parameters and laboratory assessments will be summarized in total and stratified for gender, center and study arm.

Continuous variables will be summarized using standard statistical measures, i.e. the number of observations, number of missing observations, mean, standard deviation, minimum, 1st quartile, median, 3rd quartile and maximum. Categorical variables will be summarized in frequency tables.

### Primary objective

Time to discharge will be compared using the ordinal scale, between study arms using Cox regression adjusting for site, age and gender.

Time to need of mechanical ventilation or death will be compared using the ordinal scale, between study arms using Cox regression adjusting for site and gender.

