## Primary endpoint (variable)

Primary endpoints (variables):

Time to need of mechanical ventilation or death, as a part of the clinical status as assessed by the 7-point ordinal scale up to 30 days after inclusion.

Time to discharge from hospital, as a part of the clinical status as assessed by the 7-point ordinal scale up to 30 days after inclusion

1) Not hospitalized, no limitations on activities.

2) Not hospitalized, limitation on activities;

3) Hospitalized, not requiring supplemental oxygen;

4) Hospitalized, requiring supplemental oxygen;

5) Hospitalized, on non-invasive ventilation or high flow oxygen devices;

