**Duration of supplemental oxygen (days):**

Total days of extra oxygen described as any additional oxygen given to the patient at any time during the day between 00-24.

Need of mechanical ventilation:

If the patient is in need of mechanical ventilation the date of this will be defined. Evaluated for 30 days and after 6 months.

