### Secondary objectives

Frequencies of Adverse events will be compared between the two arms using Fisher’s exact test.

Duration of supplemental oxygen (days) will compared between study arms using linear regression adjusted for gender and site.

Time to need of mechanical ventilation will be compared using the ordinal scale, between study arms using Cox regression. And the frequency of need of mechanical ventilation in the two arms will be tested using Fisher’s exact test.

Laboratory assessments at each time of measurement will be compared to baseline and extreme value and differences between study arms evaluated using linear or generalized linear regression adjusting for site, age and gender.

The change in viral load on day 2, 4 and 6 as compared to baseline will be compared between study arms. Also, the maximum decrease in viral load will be calculated, as the difference between observed value and maximal observed value, and compared between study arms. The analyses will be performed using linear regression adjusting for site and gender.

Total hospital stay (days) evaluated at 30 days and 6 months will be compared between groups using linear regression adjusting for site, age and gender.

Frequency of re-admission to hospital due to rebound COVID-19 will be compared between study arms using Fisher’s exact test.

Time to death will be compared between study arms using Cox regression adjusting for site and gender.

Hormonal status at 6 months will be compared to normal reference values and compared between study arms.

Frequency of serological immunity for Covid-19 will be compared between the study arms using Fisher’s exact test.

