### Drop-outs

In all survival analyses drop-out will be censored at time of drop-out. For all other analyses drop-outs will be excluded from the analyses.

- 1. Adjustment of significance and confidence interval

Indicate possible tests for multiple comparisons. Adjustment should always be considered for multiple primary outcomes. Specify details of any adjustment procedures or provide an explanation for why justification is not considered necessary.

Multiple testing correction will be performed using Bonferroni’s methods to adjust for having two primary outcomes.

- 1. Sample size calculations

The sample size of the full study will be determined based on data from the prolongation study.

- 1. Interim analysis (if relevant)

The primary outcomes will be evaluated after prolongation phase.

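### Oxygen days and hospital days are raw counts that stop at death, and time to discharge has no rule for patients who die, so excess deaths can be hidden or look like recovery.

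*Protocol*

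**What the plan says.** **Time to discharge.** The protocol has two primary endpoints, both read from the 7-point scale up to day 30: "Time to need of mechanical ventilation or death, as a part of the clinical status" and "Time to discharge from hospital, as a part of the clinical status". Death (category 7) is part of the first and not of the second. Section 10.2.1, Primary objective, fixes the model for discharge: "Time to discharge will be compared using the ordinal scale, between study arms using Cox regression adjusting for site, age and gender".

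**Day counts.** Section 10.2.1, Secondary objectives, states: "Duration of supplemental oxygen (days) will compared between study arms using linear regression adjusted for gender and site", and "Total hospital stay (days) evaluated at 30 days and 6 months will be compared between groups using linear regression". Section 8.1.2 defines both variables as simple counts. Oxygen is "Total days of extra oxygen described as any additional oxygen given to the patient at any time during the day", and a hospital day is any calendar day on which the patient was admitted. Neither definition mentions death.

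**Incomplete follow-up.** The only rule is under Drop-outs: "In all survival analyses drop-out will be censored at time of drop-out". In all other analyses drop-outs are left out. The text does not say whether a death is a drop-out.

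**Multiplicity.** Section 10.3 applies Bonferroni across the two primary outcomes, so either can succeed alone.

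**The concern.** A patient who dies on day 3 can contribute at most about 3 oxygen days and 3 hospital days. In a linear regression on days, that is a good score. If deaths are instead classed as drop-outs and excluded, an arm with more deaths loses more of its sickest patients, and its mean can again look better.

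Time to discharge is exposed in a different way. A Cox analysis that censors at death treats the patient as someone who would have gone on to be discharged at the same rate as those still in hospital. If the patients who die are those with the longest expected stays, removing them raises the apparent discharge rate of that arm.

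The benefit-risk section accepts that an adverse interaction with the immune response cannot be excluded. The direction in which these endpoints move when deaths increase therefore matters for reading the trial. The primary outcomes also feed the sample size decision after the prolongation phase.

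**Working it through.** The protocol gives no death rate, event rate, effect size or power, so there is no figure of its own to reproduce. From the documents come the 2:1 allocation, the 30-day window, the maximum of 600 patients and Bonferroni over two outcomes. Everything else here is assumed, including an overall two-sided alpha of 0.05 (0.025 per outcome).

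**Step 1: arithmetic for the day counts.** If survivors in both arms average m days and deaths contribute d days, the difference in means is

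difference = −(excess death proportion) × (m − d).

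- Hospital days, 5 points of excess mortality, m = 10, d = 6: −0.05 × 4 = −0.20 days.
- Hospital days, 10 points, m = 10, d = 3: −0.10 × 7 = −0.70 days.
- The first case with each death scored as 30 days: +0.05 × (30 − 10) = +1.00 day.
- Oxygen days, taking m as the days those patients would otherwise have needed: from −0.05 × (15 − 10) = −0.25 to −0.10 × (25 − 6) = −1.9 days. Oxygen days were not simulated.

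**Step 2: simulation, N = 600, 200 runs per row, no treatment effect on discharge.** A hazard ratio (HR) above 1 means faster discharge on enzalutamide. Stay differences are enzalutamide minus control, in days.

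- Setting A: 30% severe patients (mean time to discharge 40 days) and 70% mild (mean 7 days). Deaths occur only among the severe, at a daily hazard of 0.02 in control and 0.02, 0.04 or 0.08 on enzalutamide.
- Setting B: no severity mix, mean 12 days, daily death hazard 0.01 vs 0.02.
- Setting C: deaths drawn from patients who would otherwise have been discharged.

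| Setting | Deaths, control vs enzalutamide | HR, censored at death | HR, held undischarged to day 30 | Stay, raw count | Stay, deaths excluded | Stay, death = 30 days |
|---|---|---|---|---|---|---|
| A | 9.6% vs 9.8% | 0.99 | 0.99 | +0.05 | +0.06 | +0.09 |
| A | 9.6% vs 15.6% | 1.05 | 0.96 | −0.98 | −1.08 | +0.29 |
| A | 9.6% vs 21.8% | 1.13 | 0.90 | −2.15 | −2.10 | +0.79 |
| B | 9.7% vs 17.7% | 1.00 | 0.89 | −0.83 | −0.79 | +0.88 |
| C | 10% vs 15% | 1.00 | 0.93 | −0.45 | −0.43 | +0.59 |
| C | 10% vs 20% | 0.97 | 0.84 | −0.75 | −0.72 | +1.44 |
| C, no severity mix | 10% vs 20% | 0.92 | 0.80 | −0.32 | −0.02 | +1.85 |

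In the third row fewer enzalutamide patients leave hospital by day 30 (75.9% vs 81.6%), yet the censored HR favours enzalutamide. A false significant benefit at 0.025 two-sided appeared in 14.5% of runs there and in 3.5% of runs in the second row. The nominal rate in that direction is 1.25%. Across setting C at N = 100 and N = 600, the censored HR ran from 0.91 to 1.00.

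**Step 3: a second severity model.** Here 75% of patients have stays of 1 day plus an exponential with mean 6, and 25% have 3 days plus an exponential with mean 25. Deaths fall on 40% (control) or 80% (enzalutamide) of the second group. Mortality is about 7% vs 15%. The discharge HR was about 1.06 with censoring at death and 0.93 with deaths held to day 30. Mean stay was about 9.1 vs 8.1 days as a raw count, and 9.0 vs 7.7 with deaths excluded. At N = 600 a false discharge benefit occurred in about 6% of runs, and excess death was itself significant at the same level in about 64%.

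**The case against.** **The protocol does not censor deaths.** A reader might infer from the Cox model and the drop-out rule that deaths are censored at death in the discharge analysis. The documents do not say so. Discharge is read from a scale on which a dead patient never reaches a not-hospitalized category, so holding deaths as undischarged to day 30 also fits the text. A statistical analysis plan that is not shown could settle it. This objection stands: for the primary endpoint the fault is an open rule, not a wrong method. It does not cover the day counts, where the protocol itself fixes both the raw count and the linear model.

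**Death is counted elsewhere.** It is part of the other primary endpoint, it has its own Cox analysis, and the DSMB can stop randomization for safety. It would be tempting to say the trial could report success while mortality goes unseen. That is not supported, because the same report would carry those results. What remains is that nothing ties a positive discharge result to mortality, and Bonferroni lets it stand alone.

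**The false benefit is not general.** It needs deaths to fall on patients with long expected stays. In settings B and C the censored HR was at or below 1.00, so harm was hidden or understated but not reversed. This also stands.

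**Ventilation alone.** One might object likewise to "Time to need of mechanical ventilation will be compared using the ordinal scale, between study arms using Cox regression", since a patient who dies unventilated has no event. The ventilation-or-death primary endpoint already covers that case, so it is not pressed here.

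**Conclusion.** The point holds in two parts of different strength.

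- **Oxygen days and hospital days: firm.** As specified, a raw count falls when deaths rise. Under the assumed rates mean stay was 0.3 to 2.2 days shorter in the arm with more deaths. Excluding deaths gave nearly the same shift in most settings, and almost none where death was unrelated to length of stay.
- **Time to discharge: conditional.** If deaths are censored at death, the HR can hide excess mortality, or reverse it where deaths fall on long-stay patients: 1.05 to 1.13, against 0.90 to 0.96 with deaths held as undischarged. If deaths are held to day 30, the problem disappears.

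The plan should be corrected, but the harm is limited because two other analyses count death directly. All death rates, stay lengths and the alpha level are assumptions. The direction for the raw day counts depends only on deaths ending the count before the patient would have stopped using oxygen or left hospital.

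**What to change.** 1. In section 10.2.1, Primary objective and Drop-outs, state that a death is not a drop-out. State that a patient who dies before discharge stays in the risk set as not discharged, censored at day 30. Show the cumulative incidence of discharge and of death by arm.
2. For the two day counts, add days alive and free of oxygen, and days alive and out of hospital, both to day 30. Score deaths as 0, use a rank-based or proportional-odds analysis, and base conclusions on these. The raw counts can stay as description.

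**Cost.** The change is wording in section 10.2.1 and a little more analysis. Date of death, oxygen days and admitted days are already collected under section 8.1.2. If the secondary variables are formally redefined rather than supplemented, section 13 makes that a substantial change needing approval from both authorities.
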